## Abstract

(1) Background: The incidence of gestational diabetes mellitus (GDM) is rising globally. The current evidence indicates that GDM, especially in conjunction with maternal overweight, can alter the composition of infants’ gut microbiota, potentially increasing the risk of inflammatory diseases, metabolic disorders, and neurodevelopmental issues later in life. Probiotic supplantation early in life might establish eubiosis and mitigate future complications. To best of our knowledge, no study has evaluated the effects of probiotics on gut dysbiosis in the infants of mothers with GDM. (2) Methods: This study will be a single-centre, double-blind, randomized, placebo-controlled trial enrolling sixty neonates born after 35 weeks of gestation to mothers with GDM. The participants will be randomly assigned to receive either a triple-strain probiotic or a placebo for four months. The primary objective is to assess the effectiveness of probiotic supplementation in correcting gut dysbiosis in the infants of mothers with GDM at four months of age. Faecal microbiome composition shall be estimated using 16SrRNA and shotgun sequencing. The secondary outcomes will include the quantification of faecal short-chain fatty acids at birth and at four months, as well as growth and developmental assessments at four, twelve, and twenty-four months. (3) Trial registration: This trial protocol is registered (ACTRN12624000930583p) in the Australian Clinical Trials registry (ANZCTR).

## 1. Introduction

With a rising trend in obesity worldwide, the incidence of gestational diabetes mellitus (GDM) and associated pregnancy and perinatal complications have increased [1]. The pooled global standardized prevalence of GDM, based on the International Association of Diabetes in Pregnancy Study Group criteria, is 14%, with a range from 0.7% to 36.8%. This prevalence shows little variation between high- and low-income countries [2]. Following the global trend, the incidence of GDM in Australia has increased from 5.2% in 2010 to 16.1% in 2018. This increase is attributed to factors such as advancing maternal age and a growing prevalence of overweight and obesity, with 27% of women classified as overweight and 22% as obese in 2020 [3].

Intestinal microflora and their metabolites are believed to play a crucial role in body weight regulation, energy homeostasis, fermentation, and the absorption of non-digestible carbohydrates. Mothers with GDM are known to have distinct microbial profiles in their gut, vagina, oral cavity, and placenta compared to those without GDM [4]. Dysbiosis may contribute to the development of metabolic disorders, including obesity, diabetes, and GDM [5]. The mother serves as the primary source of the infant’s microbiome, with the most substantial exposure occurring during birth and the post-partum period through both vertical and horizontal transmission [6,7]. Several studies suggest that GDM alone, or together with maternal overweight can alter the composition of infants’ microbiota and may set the stage for future risk of inflammatory and metabolic diseases [8,9]. The recent evidence suggests significant dysbiosis in infants born to mothers with GDM with reduced alpha diversity and an abundance of Firmicutes and Proteobacteria [10]. The disruption of microbiota early in life is known to be associated with the later onset of inflammatory, immune-mediated, allergic, and dysmetabolic diseases [11,12]. The alterations in neonatal microbiota associated with GDM may provide valuable insights into the increase in the intergenerational prevalence of obesity and diabetes. In addition, infants of GDM mothers are also at increased risk of atypical neurodevelopment, such as autism spectrum disorder [13]. A notable decrease in Prevotella genera abundance is observed in both children with autism with gastrointestinal symptoms, as well as infants born to mothers with GDM [14,15]. This could indicate a potential physiological explanation for the higher occurrence of autism in infants born to mothers with GDM. Hence, early establishment of a eubiotic environment is imperative. We have two approaches to address early life dysbiosis: administering probiotics to either the mother, or directly to the infant. The perinatal probiotic supplementation of pregnant women regardless of GDM status may be associated with an increased risk of pre-eclampsia [16,17]. To our knowledge, no studies have examined probiotic supplementation in infants of mothers with GDM to improve their gut microbial composition or clinical outcomes. Therefore, we propose a randomized controlled trial (RCT) to evaluate the effectiveness of probiotics in influencing the gut microbial composition of infants born to mothers with GDM.

## 2. Study Materials and Methods

### 2.1. Hypothesis and Aim

We aim to assess the effects of probiotic supplementation on the faecal microbiome composition of infants of mothers with GDM. We hypothesize that probiotic supplementation with triple-strain Bifidobacteria, 1 × 10^9^ CFU of each (*Bifidobacterium breve* M-16V, *Bifidobacterium longum* subsp. *infantis* M-63, *Bifidobacterium longum* subsp. *longum* BB536), will reduce dysbiosis compared to that of the control group. This will be assessed as an increase in the abundance of beneficial bacteria (e.g., bifidobacteria) and a reduction in the abundance of pathogenic bacteria (e.g., gammaproteobacteria).

### 2.2. Rationale for Selecting the Three-Strain Bifidobacteria Product

This approach is grounded in previous studies, highlighting the benefits of multi-strain probiotics and the importance of bifidobacteria in infants [18], and our two previously published RCTs using triple-strain Bifidobacteria [19,20].

One of these trials evaluated this product against a placebo in term neonates with congenital gastrointestinal surgical conditions [20]. The median (IQR) relative abundance of potentially pathogenic families was lower, and the relative abundance of Bifidobacteriacae was higher in the probiotic versus placebo groups after two weeks of supplementation [20]. Our other RCT compared a single- vs. three-strain bifidobacterial probiotic in extremely preterm infants [19]. The time to full enteral feed (primary outcome) was similar in infants administered single vs. three-strain bifidobacteria at a dose of 3 billion CFU/day. Both the probiotics were effective in reducing dysbiosis significantly [19]. Importantly, the probiotic product used in our trials was safe, and none of the participants developed sepsis due to the administered probiotic bacteria.

### 2.3. Participants

Infants of mothers with GDM born at >35 weeks and admitted to a postnatal ward.

### 2.4. Design and Setting

Double-blind, randomized placebo-controlled trial in postnatal wards of our tertiary referral and teaching hospital in Western Australia. Refer to Figure 1 for design.

### 2.5. Eligibility Criteria

Infants will be eligible for recruitment if: gestation > 35 weeks, born to mothers with GDM, predominantly breast-fed (>80% feed as breast feed), maternal intention of breast feeding for at least 6 months, presence of informed parental consent, and resident of local metropolitan area.

### 2.6. Exclusion Criteria

Infants will be excluded if: presence of congenital malformation, chromosomal aberration, or immunodeficiency; residing outside the local metropolitan area; need for antibiotics at birth; presence of maternal chorioamnionitis or prolonged rupture of membranes (>18 h); or mothers with GDM administered antibiotics within 7 days prior to delivery.

### 2.7. Intervention

Triple-strain Bifidobacteria: 1 × 10^9^ CFU of each (*Bifidobacterium breve* M-16V, *Bifidobacterium longum* subsp. *infantis* M-63, *Bifidobacterium longum* subsp. *longum* BB536) administered from birth till 4 months of age.

### 2.8. Control

The infants will receive identical placebo sachets containing maltodextrin that match the weight and appearance of the probiotic sachet.

### 2.9. Sample Size Calculation

A sample size of 30 per group (total 60) was considered adequate to detect a 1.5-fold difference in alpha diversity with 80% power and a significance level of 0.05. By focusing on biological relevance, this sample size ensures that even subtle changes in microbial composition can be detected, providing a robust foundation for understanding the underlying biological mechanisms. This sample size allows for the detection of biologically meaningful variations in microbial composition, ensuring that differences in diversity metrics, such as Shannon diversity or Bray–Curtis dissimilarity, are statistically significant. By focusing on these well-defined biological parameters, this study can reliably capture important variations in microbial communities, providing a strong foundation for understanding their role in the system under investigation [21,22,23].

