### 2.10. Primary Outcome

Faecal microbiome composition will be estimated using 16S rRNA and shotgun sequencing. Baseline gut dysbiosis will be assessed at Timepoint 1 (T1: first week of life) by evaluating the ratio of beneficial to pathogenic bacteria, with reductions in dysbiosis measured at Timepoint 2 (T2: after four months of supplementation) in the probiotics group compared to the placebo group. The following variables will be analysed: (1) the presence or absence of specific species or pathways and clusters based on the unsupervised clustering of the gut microbial profile; (2) alpha diversity, richness, the abundance of particular species or pathways, and the differences in these numeric variables (treatment vs. baseline).

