## 4. Discussion

To our knowledge, the PRIMD trial is the first adequately powered, placebo-controlled RCT evaluating the effect of probiotic supplementation on dysbiosis in infants of mothers with GDM and the risk of probiotic sepsis.

Given the adverse effects of maternal GDM on infants’ gut microbiota and neurodevelopment, it is important to assess this outcome in our trial [38,39,40,41]. The dynamic maturation of gut microbiota during infancy is affected by various factors, including maternal health (e.g., GDM), the delivery mode, the feeding pattern, gestational age, and exposure to medications [42,43]. The disruption of initial microbial colonization has been associated with risk of adverse neurodevelopment, allergies, obesity, and auto-immune disorders in later life [44]. Gut microbiota and their metabolites regulate neurodevelopment and cognitive functioning via the bi-directional communication system known as the GMB axis [45]. The GMB axis influences brain development and function via the hypothalamo–pituitary axis (HPA); the vagus nerve; immune signalling; the production of neurotransmitters; and the production of metabolites, such as SCFAs (butyrate, propionate, and acetate), bile acids, and tryptophan derivatives. SCFAs maintain and modulate both gut epithelial and blood–brain barrier (BBB) integrity [46,47,48]. They directly affect the brain, binding to local receptors and induce epigenetic modifications, thus modulating neuro-inflammation. Additionally, SCFAs’ enhance regulatory T cell function and activate the sympathetic nervous system and the vagus nerve. Indole, a tryptophan derivative, reduces neuro-inflammation and enhances gut epithelial and BBB integrity [49]. Bile acids influence the brain and HPA axis through specific local receptor modulation [50,51]. Gut microbiota can produce serotonin, dopamine, nor-epinephrine, histamine, and gamma-amino butyric acid (GABA) directly or indirectly via entero-endocrine cell stimulation in the gut epithelium. Bifidobacteria are known to produce GABA [52]. These neurotransmitters exert local effects through vagal stimulation and can directly affect the brain by traversing the BBB [53].

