## 5. Conclusions

We believe our innovative trial assessing the effects of probiotic supplementation on dysbiosis in the infants of mothers with GDM will provide robust data on gut microbiota, faecal short-chain fatty acids, long-term growth, and neurodevelopmental outcomes to guide adequately powered robust RCTs in this field.

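### The power statement covers alpha diversity alone, cannot be verified, and does not support the claim that subtle changes will be detected

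*Protocol article*

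**What the plan says.** Section 2.9 contains the only power calculation in the article: "A sample size of 30 per group (total 60) was considered adequate to detect a 1.5-fold difference in alpha diversity with 80% power", at a significance level of 0.05. The Abstract plans to enrol the same number, sixty. Section 2.9 then adds that "this sample size ensures that even subtle changes in microbial composition can be detected", and that differences in metrics such as Shannon diversity or Bray–Curtis dissimilarity will reach statistical significance.

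Section 2.1 tests the hypothesis through higher abundance of beneficial bacteria and lower abundance of pathogenic bacteria. Section 2.10 assesses dysbiosis "by evaluating the ratio of beneficial to pathogenic bacteria", looks for its reduction at T2 (four months), and then lists variables to be analysed. Alpha diversity is on that list, with richness, abundances of particular species or pathways, and clusters.

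Section 3.7 makes all tests two-sided at 0.05 and names Mann–Whitney for univariate comparisons of continuous data.

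The Discussion describes the trial as an "adequately powered, placebo-controlled RCT evaluating the effect of probiotic supplementation on dysbiosis in infants of mothers with GDM and the risk of probiotic sepsis". The Conclusions say its data will serve "to guide adequately powered robust RCTs in this field".

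**The concern.** There are three separate problems.

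- **Coverage.** The power figure is attached to one listed variable. The measure by which section 2.10 assesses dysbiosis, and the abundances by which section 2.1 tests the hypothesis, have none.
- **Verifiability.** A fold difference yields a sample size only once a scale and an SD are fixed. Section 2.9 states neither. It names no index and states no allowance for missing four-month stools.
- **Sensitivity.** The assurances about subtle changes and about significance go beyond the calculation they follow. Power is the probability of a significant result under a specified effect; no sample size makes differences significant.

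A reader who takes these statements at face value could read a null result on the ratio as evidence that the probiotic does not change dysbiosis, when moderate effects would more likely be missed than found. The Discussion sentence, as worded, could also lead a reader to treat an absence of sepsis cases as an adequately powered safety result.

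**Working it through.** **Inputs from the document**
- 30 per group, 1:1; 1.5-fold difference in alpha diversity; 80% power; level 0.05 (section 2.9).
- Two-sided tests; Mann–Whitney for continuous data (section 3.7).
- SD of alpha diversity: not stated. Loss: not stated.

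**Inputs assumed**
- Asymptotic relative efficiency of Mann–Whitney against the t-test: 0.955 (normal data on the analysis scale).
- Log-scale SDs of 0.4 to 0.8 and losses of 10% to 30%, used only to show ranges.

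**1. Can the plan's figure be reproduced?** Not forward, because the SD is missing. The formula can be inverted to give the smallest standardized difference d detectable with 30 per arm:
- Normal approximation: d = (1.960 + 0.842) × √(2/30) = 0.72.
- Noncentral t: d = 0.736.
- Mann–Whitney, effective n = 30 × 0.955 = 28.65 per arm: d = 0.753.

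**2. What SD does the 1.5-fold claim imply?**
- Log scale: ln(1.5)/0.736 = 0.405/0.736 = 0.55.
- Raw scale: (0.5 × control mean)/0.736, so the SD is about 68% of the control mean.

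**3. How much does the answer depend on that SD?** Power for a 1.5-fold difference, 30 per arm, t-test:

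| Assumed log-SD | d = 0.405/SD | Power |
|---|---|---|
| 0.4 | 1.01 | 97% |
| 0.5 | 0.81 | 87% |
| 0.55 | 0.74 | 80% |
| 0.6 | 0.68 | 73% |
| 0.7 | 0.58 | 60% |
| 0.8 | 0.51 | 49% |

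The stated 80% is compatible with the design, but so are much higher and much lower values.

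**4. Is the claim about subtle changes true?** This needs no SD, because the effects are in SD units. Power with 30 per arm, t-test:

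| d | Power | n per arm for 80% (normal approximation) |
|---|---|---|
| 0.5 | 48% | 63 |
| 0.4 | 33% | 99 |
| 0.3 | 21% | 175 |
| 0.2 | 12% | 393 |

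The claim fails for any continuous measure, whatever its SD.

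**5. What if four-month samples are missing and enrolment stays at 60?**

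| Assumed loss | n per arm | Power at d = 0.736 (t-test) | Detectable d, t-test | Detectable d, Mann–Whitney |
|---|---|---|---|---|
| 0% | 30 | 80% | 0.74 | 0.75 |
| 10% | 27 | 76% | 0.78 | 0.80 |
| 20% | 24 | 70% | 0.83 | 0.85 |
| 30% | 21 | 64% | 0.89 | 0.91 |

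**6. Sepsis.** With no case among 30 exposed infants, the exact two-sided 95% upper limit is 1 − 0.025^(1/30) = 11.6%.

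**The case against.** The strongest reply is that section 2.10 itself lists alpha diversity among the primary-outcome variables, so the calculation does address the primary outcome. That stands. A reader might infer that the trial was powered on something outside its primary outcome, and the text does not support this. Section 2.10 names no single deciding endpoint, and its wording ties the ratio to the baseline assessment before turning to reductions in dysbiosis at T2. What remains is that the power figure covers one of several variables, and neither the ratio nor the abundances in the hypothesis.

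Second, missing inputs do not prove a shortfall. A reader might infer that the trial is underpowered, but for alpha diversity the table above runs from 97% to 49% over the assumed SDs. The adequacy claim is unsupported, not shown to be false.

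Third, this is a condensed article, and section 2.9 cites sources that may hold the SD. The full protocol may also deal with losses. So the right statement is that no allowance is stated, not that none exists. This does not rescue the sensitivity claims, which the article makes itself and which fail in SD units.

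Two tempting extensions should not be used as evidence. Detectable fold differences for the ratio need SDs that the article does not give, and the 1.5-fold figure was never claimed for the ratio. Constructed examples in which more bifidobacteria lower Shannon diversity depend on an invented starting composition.

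Finally, the sepsis wording is one loose sentence in the Discussion. Section 2.9 makes no power claim for sepsis and section 2.14 calls it rare, so this is an editorial correction and not a design fault.

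**Conclusion.** The point holds in this form. The 80% power statement applies to alpha diversity, one of several primary variables, and cannot be verified from what is stated. It is exact only at a log-scale SD of about 0.55. The ratio and the hypothesis abundances have no power statement.

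The claim that subtle changes are detectable is contradicted by calculation: 30 evaluable infants per arm detect about 0.75 SD with Mann–Whitney, and power at 0.3 to 0.5 SD is 21% to 48% (t-test). The assurance of statistical significance is wrong at any sample size.

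Calling the trial adequately powered is unsupported for the ratio and for sepsis, and sits badly with the Conclusions, which present the trial as a guide to later adequately powered ones.

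These figures assume a single comparison at two-sided 0.05, roughly normal data on the analysis scale, and all 60 infants giving a usable T2 sample. The loss figures are illustrations. None of this shows that 60 infants are too few for alpha diversity.

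**What to change.** Keep 60 infants and rewrite section 2.9. Suggested content: thirty evaluable infants per arm give 80% power (two-sided 5%, Mann–Whitney) for a difference of about 0.75 SD in any continuous microbiome measure at T2, including the log ratio of beneficial to pathogenic bacteria; if 20% of T2 samples are missing (assumed), the detectable difference is about 0.85 SD.

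Also:
- State the index, scale and SD, with its source, behind the 1.5-fold alpha-diversity figure.
- Delete the claim about subtle changes and the assurance that differences will be statistically significant.
- Remove the adequately powered description from the Discussion, at least as it applies to sepsis, and report sepsis descriptively.

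No change to recruitment, sampling or assays is needed. The cost is that the stated sensitivity becomes less favourable, and that the trial team must find and report the SD it relied on.

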### 2.10. Primary Outcome

Faecal microbiome composition will be estimated using 16S rRNA and shotgun sequencing. Baseline gut dysbiosis will be assessed at Timepoint 1 (T1: first week of life) by evaluating the ratio of beneficial to pathogenic bacteria, with reductions in dysbiosis measured at Timepoint 2 (T2: after four months of supplementation) in the probiotics group compared to the placebo group. The following variables will be analysed: (1) the presence or absence of specific species or pathways and clusters based on the unsupervised clustering of the gut microbial profile; (2) alpha diversity, richness, the abundance of particular species or pathways, and the differences in these numeric variables (treatment vs. baseline).

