### 2.11. Secondary Outcomes

Faecal short-chain fatty acids (SCFAs) and bile acids will be quantified in the first week of life (T1), and again four months after probiotic supplementation (T2). Growth parameters, including weight, length, and head circumference, will be assessed at 4 (T2), 12 (T3), and 24 (T4) months of age. Developmental parameters will be evaluated using the Ages and Stages Questionnaire (ASQ) and the ASQ-Social Emotional scale, 2nd version, at 4, 12, and 24 months of age.

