### 2.17. Probiotic Protocol

Enrolled neonates will be supplemented with the freshly reconstituted contents of the allocated sachets every day, which will be continued till four months of age. The dry, lyophilized powder in the sachets will be reconstituted using the mums’ own milk (first choice) or sterile water for injection. The dose will be 3 × 10^9^ CFU/day (1 mL reconstituted solution twice daily). Supplementation will be temporarily withheld if vomiting, diarrhea, or abdominal distension is noted.

The manufacturer, Morinaga Milk Industry Co., Ltd., are not a sponsor and will only supply the probiotic and placebo free for the trial and are not involved in the design, conduct, analysis, and reporting of the trial.

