### 3.1. Faecal Sample Collection

Stool samples will be collected from the diaper at two time points in sterile containers from each infant. The first sample (T1) will be collected as soon as possible after birth/admission to the postnatal ward (week 1). The second sample (T2) will be collected at the age of 4 months. All the samples will be labelled, weighed, and stored at −80 °C. After completing recruitment, the samples will be shipped on dry ice to the laboratory for storage at −80 °C and analyses. Acidified samples (5-fold in 1% phosphoric acid) will be shipped on dry ice to the laboratory for SCFA analysis.

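### Bifidobacterium DNA from the sachets can raise the T2 dysbiosis ratio with no change in the resident flora; a companion measure on non-Bifidobacterium reads would show whether anything else moved

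*Protocol article*

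**What the plan says.** **Outcome.** Section 2.10 assesses dysbiosis by "evaluating the ratio of beneficial to pathogenic bacteria", comparing the arms at T2. It does not list the taxa on either side of the ratio. Section 2.1 says how reduced dysbiosis will be recognised: "an increase in the abundance of beneficial bacteria (e.g., bifidobacteria) and a reduction in the abundance of pathogenic bacteria (e.g., gammaproteobacteria".

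**Product and dosing.** All three strains are Bifidobacterium (section 2.7), "administered from birth till 4 months of age". Section 2.17 has daily dosing, "which will be continued till four months of age". The placebo is maltodextrin (section 2.8).

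**Sampling.** Section 3.1: "Stool samples will be collected from the diaper at two time points". The first is in week 1. For the other: "The second sample (T2) will be collected at the age of 4 months". No stool is planned after that.

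**Wording of T2.** Section 2.10 has "T2: after four months of supplementation", which agrees with section 3.1. Section 2.11 has "again four months after probiotic supplementation (T2", which taken literally is a different time, although the same section also places T2 at 4 months of age.

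**Laboratory.** DNA is extracted from whole stool (section 3.2). It is profiled by 16S V3–V4 (section 3.6.1) and by shotgun reads at species level, with subspecies calls for *B. longum* only (section 3.6.4). No step is described that separates product strains from resident bifidobacteria, or passing cells from colonisers.

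**The concern.** The genus being given is the named example of the bacteria that count in the infant's favour, and the stool is taken at the age at which dosing ends, with no stated washout. The readout is made of relative abundances, so added product reads act twice: they increase the beneficial share and dilute the pathogen share. Both parts of the section 2.1 definition then move the favourable way even if no resident organism has been gained or lost.

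The stated objective in the Abstract is to correct dysbiosis. A higher ratio on its own would be compatible with that, with colonisation by the product, or with product passing through. The report would need some way to say how far the result goes beyond the presence of bifidobacteria.

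**Working it through.** The plan gives no figure for the ratio to reproduce. The sample size in section 2.9 is for alpha diversity and does not bear on this point.

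**1. Effect of product reads on the ratio.** Let *b* and *g* be the resident beneficial and pathogenic shares, and *f* the share of T2 reads that come from the product. All three are assumptions. With the resident flora unchanged:

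- ratio without product = b / g
- ratio with product = (b(1−f) + f) / (g(1−f))
- relative rise = f / (b(1−f)), which does not depend on g
- pathogen share with product = g(1−f), a relative fall of exactly f

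Example, b = 0.40, g = 0.20, f = 0.10: (0.36 + 0.10) / 0.18 = 2.56 against 2.00, a rise of 28%.

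| Resident b / g | No product | f = 5% | f = 10% | f = 20% |
|---|---|---|---|---|
| 60% / 10% | 6.00 | 6.53 (+9%) | 7.11 (+19%) | 8.50 (+42%) |
| 40% / 20% | 2.00 | 2.26 (+13%) | 2.56 (+28%) | 3.25 (+63%) |
| 20% / 30% | 0.67 | 0.84 (+26%) | 1.04 (+56%) | 1.50 (+125%) |

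**2. What product share is plausible?** The dose is 3 × 10^9 CFU/day (section 2.17). The rest is assumed: stool density 10^9 to 10^11 bacteria per gram, stool mass 10 to 100 g/day, product DNA 1 to 10 times the labelled CFU, and all of it excreted. Then f = product / (product + density × mass), which runs from about 0.03% to 75%. At 10^10 per gram and 30 g/day, f is 3×10^9 / (3×10^11 + 3×10^9) = 1% at labelled CFU and 3×10^10 / (3×10^11 + 3×10^10) = 9% at ten times that. The documents do not narrow this range.

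**3. Chance of p < 0.05 from product DNA alone.** Simulation with 30 per arm, no change in resident flora, and a two-sided Mann–Whitney test on the Bifidobacterium-to-pathogen ratio (the test that section 3.7 gives for continuous data). Assumed: resident bifidobacteria vary with a logit SD of 1 or 2; pathogens have a median of 20% of the remaining reads, logit SD 1; 1,000 trials per setting. With f = 0 the rate was 4% to 6%, as it should be. Ranges below cover the two SDs.

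| Median resident bifidobacteria | f = 1% | f = 3% | f = 10% | f = 25% |
|---|---|---|---|---|
| 1% | 55–78% | 96–99.6% | 100% | 100% |
| 10% | 6% | 17–19% | 58–81% | 96–100% |
| 40% | 4–6% | 5% | 12–14% | 40–60% |
| 60% | 4–5% | 6% | 8% | 22–33% |

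**4. A measure that product DNA cannot move.** Let *B* be the resident Bifidobacterium share. Gammaproteobacteria as a share of non-Bifidobacterium reads is g(1−f) / [(1−f)(1−B)] = g / (1−B) for any f. The same algebra shows its blind spot: if colonising bifidobacteria take a share of the community and displace all other taxa in proportion, the factor cancels again and the measure does not change.

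**The case against.** **Raising bifidobacteria is the declared hypothesis.** Section 2.1 says so, and section 2.12 gives a reason for the timing: the infants are still on a milk-only diet. This stands. Sampling at 4 months is defensible, and the point concerns only what a higher ratio may be said to show.

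**The ratio's taxa are not fixed.** A reader might infer that its numerator is the administered genus. Section 2.10 does not say that, and section 2.1 gives bifidobacteria only as an example. Nor is the interval from the last sachet to the T2 stool fixed. A broader numerator means a larger b, and hence a smaller relative rise.

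**The trial has other evidence.** A reader might infer that it cannot tell product detection from reduced dysbiosis at all. That goes too far. Short-chain fatty acids and bile acids (section 2.11) are metabolites that product DNA does not itself raise, and beta diversity (section 3.6.2) describes the whole community, although it too can shift with product reads.

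**The artefact may be small here.** Eligibility requires predominantly breast-fed infants (section 2.5), in whom abundant resident bifidobacteria are plausible. At 60% resident, a 10% product share gives significance in about 8% of trials against a nominal 5%. This also stands.

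**A full protocol or analysis plan may add sensitivity analyses.** True, and the lack of one is not the complaint. Dosing end, stool timing and the reading of reduced dysbiosis are all fixed in the article, and together they leave the ratio open to this effect.

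**Conclusion.** The concern holds as a possible artefact and a cheap improvement. Product DNA in the T2 stool can raise the ratio and dilute the pathogen share without any change in the resident flora. The rise is 9% to 42% at 60% resident beneficial reads, 13% to 63% at 40% and 26% to 125% at 20%, for assumed product shares of 5% to 20%. A high chance of a significant result from product DNA alone needs few resident bifidobacteria or a large product share.

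The tempting stronger reading, that sachet DNA by itself will deliver a positive primary result, is not supported: the product and resident shares are not in the documents, and several plausible combinations leave the error rate near 5%. Nor does the wording of T2 in section 2.11 establish a washout, since sections 2.10, 2.11 and 3.1 all put T2 at 4 months of age or after four months of dosing.

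**What to change.** 1. In section 2.10, pre-specify next to the T2 ratio a between-arm comparison of gammaproteobacteria as a share (or log-ratio) of all non-Bifidobacterium reads. Report it as a key supportive analysis, not as a condition for success.
2. State the reading in advance. If only the ratio differs, describe the result as higher bifidobacteria (product detection or colonisation), not as a demonstrated change in the rest of the community.
3. The ratio with the administered species and subspecies removed may be shown as exploratory only, because it also removes true colonisation and resident strains of the same taxa in both arms.
4. Reconcile the wording of T2 in section 2.11 with sections 2.10 and 3.1.

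Cost: a few sentences and one extra run on sequence data already planned, with no change to dosing, visits or samples. The text should be fixed before T2 data are seen, since adding the measure afterwards would be post hoc. The downside is that it can miss a benefit in which bifidobacteria displace all resident taxa in proportion, which is why it should not be a gate.
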